### 1.3. Spatial Navigation in Alzheimer’s Disease

AD is a multifactorial neurodegenerative disease, resulting from complex interactions between genetic and environmental factors, that remains the leading cause of dementia to date. The proportion of people aged 65 years and over is growing rapidly worldwide, and it is estimated that by 2060, this age group will account nearly for 24% to 29% of the population in Western Europe and the United States [27], representing a health emergency due to social and sanitary costs. AD is characterized by progressive deterioration of cognitive functions, with episodic memory loss and spatial disorientation as the main hallmarks. No causal therapies for AD are currently available, although drug treatment efforts are progressing [28]. Thus, advances in biomarkers and behavioral tests for identifying individuals at increased risk of developing AD represent a crucial target of current research and therapeutics. Spatial navigation, or the ability to determine and maintain a trajectory from one place to another, gradually declines in the course of physiological aging [29,30,31], and spatial disorientation (SD) represents a core feature of pathological aging, especially AD [32]. Although cognitive decline precedes overt AD, pathological changes may even begin years before there are any overt behavioral impairments, and new treatments are being sought to modify this process [33]. Indeed, it has been proposed that subjective cognitive decline (SCD) (i.e., a self-experienced decline without objective cognitive impairment) might appear at the end of the preclinical phase of AD [34]. SN complaints are frequent symptoms not only in AD but also in SCD and MCI, and can be detected by specifically designed questionnaires [35] or by virtual and real-world navigation tasks [36]. SCD is gaining increased prominence in neurodegenerative research as a potential marker for future mild cognitive impairment (MCI) due to AD [37], a condition that represents the prodromal state of dementia associated to the disease. Approximately 90% of MCI patients with pathologic cerebrospinal fluid biomarker levels at baseline develop AD within 9 to 10 years [38]. Deficits in spatial orientation appear early in the course of the AD continuum [16]. AD is mainly characterized by the presence of beta-amyloid protein plaques and neurofibrillary tangles of hyperphosphorylated tau protein. According to Laczó et al. [7], amyloid-β accumulation first emerges in the neocortical regions and, early on, affects the retrosplenial cortex, while tau pathology first emerges in the transentorhinal cortex (Braak stage I) and spreads to the posteromedial entorhinal cortex and the hippocampus (Braak stage II and III) and finally to the posterior cortical regions (Braak stage IV). Neurodegeneration and brain atrophy parallel the pattern of tau pathology spreading [39]. Degeneration of the entorhinal cortex as a critical brain district supporting SN represents an initial stage of typical AD [40], and a profound loss of its neurons occurs in very mild AD [41]. Neurofibrillary AD pathology in the entorhinal cortex and hippocampus also represent the neuropathological substrate of memory decline [42] and defective PPI [43]. Finally, tau abnormalities in the entorhinal cortex can already be observed in adults under the age of thirty [44], especially in those carrying the Apolipoprotein-E(APOE)-ε4 allele [45].

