## 2. Materials and Methods

### 2.1. Design, Study Population, Recruiting Centers and Trial Registration

This is a multi-center prospective observational study. A sample of outpatients with SCD and MCI due to AD will be enrolled from three sites in Lombardy (Italian Region): “San Gerardo” Hospital (Monza), “Luigi Sacco” University Hospital (Milan), and Fondazione IRCSS Ca’ Granda Ospedale Maggiore Policlinico (Milan, Italy).

Individuals with SCD will be detected according to Jessen and colleagues’ criteria [79] while prodromal AD will be defined according to Dubois and colleagues’ criteria [80], respectively. Healthy older adults will be enrolled through advertisements distributed in social centers for senior citizens in Milan (Italy) and through popular science events (conferences, webinars) concerning research in AD prevention. The three sites currently use the neuropsychological batteries reported in the Appendix A. Healthy older adults will be assessed by the experimenters at the Department of Psychology, Catholic University (Milan, Italy), by adopting the same neuropsychological battery as the IRCSS Ca’ Granda Ospedale Maggiore Policlinico (Milan, Italy). Family medical history of AD was collected during clinical interview along with laboratory tests results and neuroimaging findings for outpatients with SCD and MCI due toAD.

For the whole sample, inclusion criteria will involve the following: age from 65 to 85 years; education not less than 5 years; basic ICT skills. All participants will be excluded from the study according to the presence of visual, hearing, or motor impairment significantly interfering with SN tasks; neurological/psychiatric disease or other medical conditions preventing SN; history of alcohol or drugs addiction; intake of psychotropic drugs; and presence of dementia. Recruitment will end on 29 February 2024.

With the aim of obtaining results that can be generalized, sociodemographic and clinical features of the sample to be recruited will be analyzed among the research team members prior to the sample enrollment according to epidemiological studies carried out on the Italian elderly population, specifically including MCI patients [81,82,83] and individuals with SCD [84].

The Uniform Resource Locator for the clinical trial registration is the following one: https://classic.clinicaltrials.gov/ct2/show/NCT05944601 (identifier: NCT05944601) (accessed on 13 July 2023).

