The participants are asked to complete a path from a start point (Figure 4, green point) to a destination point (Figure 4, blue point) in *Route A* (80.5 m) (Figure 4, dotted red line, on a scale of 1 to 500) in the PIME outdoor garden under the experimenter’s guidance. An interfering cognitive task mimicking distracting urban stimuli (e.g., people chattering, cars horns, background noise, pedestrian crossing, recognizing someone on the street, receiving a phone call, etc.) will be provided by a smartwatch worn by the participants, who are required to touch the screen when it displays a specific colored shape among different shapes presented with an interval of 15 s from each other. During this path, they are also required to remember all the existing landmarks as a cognitive exercise useful for the evaluation of spatial episodic memory. Once at the destination, they are asked to put in order the encountered landmarks (Figure 5), randomly presented as a written naming list on the experimenter’s smartphone App. In case of a sudden technology breakdown, an algebraic calculation (i.e., “*Please, subtract 7 from 100 and keep going until I stop you*”) and a different landmarks reordering (i.e., presentation with flash cards) will be provided by the experimenters as replacements. The landmarks will be mixed up with distractors in order to detect hits and false alarms. Then, they are required to navigate back to the original start point using the same route. This first task requires participants to predominantly utilize an egocentric strategy based on a navigator-centered representation of the environment.

Later, the participants will be required to reach the destination point of the encoded *Route A* again. However, at the first intersection of the way back (Figure 4, purple asterisk), unknown to them, they will be asked to find an alternative route to come back (*Route B^1^*, 94 m; *Route B^2^*, 78.5 m; *Route B^3^*, 74 m) that does not overlap with *Route A* at all (Figure 4, dotted black lines). This second task requires participants to predominantly utilize an allocentric strategy based on a formed cognitive map of the garden.

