In addition to the experimenter visually identifying and recording the frequency of the MsH with a stopwatch and a pre-set paper grid, we will measure this variable more objectively using the Howdy Senior integrated accelerometer. For this purpose, we will use the motion sensor of the sensorial body measuring the individual’s linear acceleration in the three axes (i.e., x, y, z). To segment the magnitude signals, according to Schaat et al. [88], we will adopt time intervals of 10 s, with an overlap of 5 s between subsequent intervals because a 10 s segment is sufficiently long to capture multiple steps during walking, thus revealing important behavioral changes. In this way, we will detect the MsH as a signal flattened along the three axes. Further, given that physiological parameters may alter depending on the MsH, we will also investigate the relationship between step variability and co-occurring time-dependent cardiac and respiratory parameters detected by the Howdy App, expressed as mean values, via Pearson’s correlation coefficients or their non-parametric equivalent (i.e., Spearman’s rank order correlation). Moreover, we will run a one-way ANOVA (or its non-parametric equivalent) to compare performances of the three subgroups on gait parameters collected through the Aptive app and the SSNC questionnaire. In order to explore potential association between specific neurocognitive functions and SN impaired abilities, Pearson correlations or their non-parametric equivalent (i.e., Spearman’s rank order correlation) will be further performed between the AppleGame/DNT-mv results and the neuropsychological tests used in the sending centers, especially visual–constructive skills and executive functions (see Appendix A). Given the difference of the neuropsychological battery used in the sending centers, we will group tests according to the primary cognitive domain involved and we will divide the scores obtained in a dichotomous way for each participant according to the reported cut-off values in the test manuals, i.e., 0 = pathological performance; 1 = normal performance.

Finally, a linear/generalized linear regression analysis will be run, taking into account the drop errors of the AppleGame subtasks—considered one at a time—as independent variables, and the total number of “wrong turns” (WTs)/total number of “moments of hesitation” (MsH) (in seconds) of the DNT-mv as dependent variables.

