## 3. Discussion

In relation to the first endpoint, we expect that patients with MCI due to AD will show significantly more SN deficits than healthy controls and individuals with SCD, both in the AppleGame and in the DNT-mv, in terms of higher drop errors on BPI, LPI, and PPI and higher amounts of WTs and MsH, respectively. Virtual and ecological deficits may reflect a cognitive inefficiency of the entorhinal cortex, where AD neuropathology manifests early [25]. It has also been demonstrated that virtual and ecological SN tasks can detect the SN alteration of amyloid-positive MCI patients [89,90]. According to Colmant et al. [91], we also presume that APOE-ε4 carriers will report a PPI deficit in the VR task differently from non-carriers, regardless of subgroup.

Furthermore, we also anticipate that significant physiological parameters modifications (particularly, respiratory function) may be particularly associated with MsH, given that anxiety rather than depression significantly influences SN abilities in non-demented elders [92]. Starting from difficulties in spatial orientation evaluated in naturalistic experiments able to modify gait [93], we finally assume that patients with MCI due to AD will perform worse than SCD and healthy controls in terms of “Time” and “Speed”, and report significant differences in “Direction”, all variables collected by the Howdy Aptive app in the open-space naturalistic task.

In relation to the second endpoint of the research, we assume that the drop errors obtained in the VR task may predict the route disorientation scores of the naturalistic task. In particular, we expect a causal relationship between the BPI drop error of the AppleGame and the *Route A* return path of the DNT-mv, as well as between the LPI drop error of the AppleGame and the *Route B* return path of the DNT-mv, because they mainly rely on egocentric and on allocentric navigation, respectively. A recent systematic review and meta-analysis [44,94] has outlined that the association of navigational tasks performed in virtual and real environments needs to be deeply clarified. In light of this, we believe that the AppleGame could represent a validated technique with which to detect, in laboratory, early SN deficits in populations at risk of dementia conversion to provide high-quality, time-limited diagnosis. It is a cost-effective tool able to predict real-life SN impairment that should be routinely used in clinical practice.

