The Howdy Senior system has been recently implemented by the “Aptive” App capable of recording GPS data during the naturalistic experiment. These data include “Time” as the number of minutes to complete the route; “Latitude”, “Longitude”, “Altitude”, and “Speed” as estimated by the body integrated accelerometer for calculating steps variability; and “Direction” corresponding to gait orientation with values ranging from 0° to 360°, where 0° corresponds to the north, 90° to the east, 180° to the south, and 270° to the west. Thanks to the Aptive App, a GPX tracking of participants’ body movements around the urban environment will be registered, too.

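### The three-group test for gait parameters and the SSNC is an unadjusted one-way ANOVA, although the plan's own sizing model includes age and APOE

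*Protocol article*

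**What the plan says.** All places are in the protocol article.

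- **Test.** Section 2.4 fixes the method for the gait parameters and, in the same sentence, for the SSNC: "we will run a one-way ANOVA (or its non-parametric equivalent) to compare performances of the three subgroups on gait parameters collected through the Aptive app". No covariate is named.
- **Sizing model.** Section 2.4 bases the 76 participants on a multiple regression with three predictors: age, APOE genotype and group. No analysis described later in that section contains those terms together. Its only regression uses AppleGame drop error to predict wrong turns and moments of hesitation.
- **Age.** Section 1.3 says that spatial navigation "gradually declines in the course of physiological aging". Section 2.1 admits "age from 65 to 85 years".
- **Sources.** Section 2.1 takes the SCD and MCI groups from three hospital sites, whereas "Healthy older adults will be enrolled through advertisements distributed in social centers for senior citizens in Milan" and through popular science events. No matching is stated. Sociodemographic features are to be examined before enrolment, but for generalisability.
- **Expectation.** Section 3 says "we finally assume that patients with MCI due to AD will perform worse than SCD and healthy controls in terms of" Time and Speed.
- **Time.** The text after Table 1 defines it "as the number of minutes to complete the route". In the second part of the naturalistic task (section 2.3.2), "they will be asked to find an alternative route to come back", and the three alternatives measure 94, 78.5 and 74 m.

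**The concern.** A one-way ANOVA attributes every difference between group means to group membership. By the plan's own account age influences navigation, and nothing stated keeps the three groups alike in age. If MCI patients turn out older than controls, they would be slower for that reason alone, in exactly the direction that section 3 predicts. The plan recognises age as a predictor when it sizes the study and then drops it from the stated group test. The non-parametric fallback cannot carry it either. At stake is whether a significant result on Time, Speed or the SSNC can be read as an effect of cognitive status.

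A smaller matter concerns Route B. Because Time is not scaled to distance and participants find their own way back, a longer Time may mean a longer path, a slower walk, or both.

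**Working it through.** **The plan's own figures.** The plan gives no power or error figure for this ANOVA. The only figure in section 2.4 is the sample size. With its stated inputs (f² = 0.15, α = 0.05, power 0.90, three predictors) the noncentral F calculation gives 99, not 76. That is a separate matter and does not decide this point; 76 is used below only as the planned total.

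**Inputs for the age check**

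- From the abstract: groups of 25 controls, 25 SCD and 26 MCI.
- Assumed, because the documents give none of these: no true group effect, age SD of 5 years within groups, age-outcome correlation r = 0.3, and MCI patients 3 or 5 years older than controls.

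**Step 1, spurious difference.** d = r × gap / SD.

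- 3 years: 0.3 × 3/5 = 0.18
- 5 years: 0.3 × 5/5 = 0.30

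**Step 2, noncentrality.** λ = Σ nᵢ(μᵢ − μ̄)², in units of the outcome SD.

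- Only MCI shifted: λ = d² × (50 × 26/76) = 17.105 d², that is 0.554 and 1.539.
- SCD midway: the mean is (12.5 + 26)d/76 = 0.5066d, so λ = 12.747 d², that is 0.413 and 1.147.

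**Step 3, rejection rate** of the F test on 2 and 73 degrees of freedom at a nominal 5% (critical value 3.122):

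| Age gap | SCD midway | Only MCI shifted |
|---|---|---|
| 3 years | 8.1% | 9.2% |
| 5 years | 14.2% | 17.6% |

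**Step 4, simulation** (3,000 runs per setting, SCD midway, age SD 5 years):

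| Age gap | Unadjusted, r = 0.3 | Unadjusted, r = 0.5 | With age as covariate |
|---|---|---|---|
| 0 years | 4% | 5% | 4–5% |
| 2 years | 6% | 8% | 4–5% |
| 3 years | 8% | 14% | 5% |
| 5 years | 14% | 33% | 4–5% |

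The inflation appears only with an age gap, and age as a covariate removes it.

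**Route B.** 94/74 = 1.27 and 94/78.5 = 1.20. At equal pace the longest alternative takes 27% more time than the shortest. The 20 m difference is 17 to 25 s at assumed speeds of 1.2 to 0.8 m/s.

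In a simulation with the same walking speed in every group (assumed mean 1.0 m/s, SD 0.15), the ANOVA on Time rejects in 5% of runs if all groups use the same mix of routes. If 50%, 60% or 80% of MCI patients take the 94 m route, against one third of the others, it rejects in 9%, 18% and 47%. The ANOVA on Speed stays at about 5% throughout. Route A has one length (80.5 m), so the question does not arise there.

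**The case against.** **The age bias is hypothetical.** The documents report no ages by group, no SD and no age-outcome correlation, and the full protocol might provide for matching. This stands: the bias is conditional, and the rates above illustrate rather than predict. It does not remove the point, because the stated test has no safeguard and age is known for every participant.

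**Covariate lists are commonly left to an analysis plan.** In general they are. Here, however, the article names a specific method that cannot hold a covariate, in the same section as a sizing model that has them.

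**These outcomes are not the leading ones.** Section 1.7 speaks of exploring differences, section 3 puts drop errors, wrong turns and hesitations first, and the SSNC has no stated hypothesis. This limits the weight of the point.

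**Route length is not a confounder.** A reader might infer that the unequal routes bias Time, Speed and the SSNC alike. The documents do not support that. Speed is already a rate and the SSNC is a questionnaire, so route length does not act mechanically on either. Route choice also comes after group membership. If it is unrelated to group, it adds noise and the test keeps its level. If it is related to group, the longer Time is a consequence of group behaviour and may be part of the navigation deficit. What remains is a question of interpretation: Time mixes path length with pace.

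**Wrong turns and hesitations do not need a route-length offset.** A reader might extend the point to them as unequal exposure. They are not outcomes of this ANOVA, section 2.4 gives the hesitation total in seconds, and nothing shows that the opportunity for a Route B wrong turn (overlap with Route A or leaving the walkways) grows with the metres walked.

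**Conclusion.** The point holds in a limited form. The stated group test for the Aptive gait parameters and the SSNC omits age and APOE, although the plan sizes the study with both and itself links age to navigation. With MCI patients 3 to 5 years older, an age SD of 5 years and a correlation of 0.3, all assumed, the false-positive rate is about 8% to 18% instead of 5%. With no age gap there is no inflation. It would be wrong to conclude that the comparison will be biased; the documents show only that it is unprotected.

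For Route B, the alternatives differ in length by up to 27%, so Time alone cannot separate path from pace. This is secondary and concerns Time only. The change is worth making before analysis but does not affect the feasibility of the study.

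**What to change.** In section 2.4, replace the one-way ANOVA for these outcomes with a linear model of group (two dummy variables) plus age and APOE-ε4 status, and test the two group terms jointly. If residuals are non-normal, keep this model with robust or bootstrap standard errors rather than switching to a rank test that cannot adjust. Age is the term that removes the bias shown above; APOE brings the test into line with the sizing model.

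For Route B, keep Time as recorded, also report it per metre or by chosen route, and tabulate route choice by group. The tabulation matters because a group difference in route choice may be a finding in its own right.

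The cost is small. Residual degrees of freedom fall from 76 − 3 = 73 to 76 − 5 = 71. Age and APOE genotype are already collected, and the GPX tracks can show the chosen route. The rest is a change of wording.

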## Abstract

Spatial navigation (SN) has been reported to be one of the first cognitive domains to be affected in Alzheimer’s disease (AD), which occurs as a result of progressive neuropathology involving specific brain areas. Moreover, the epsilon 4 isoform of apolipoprotein-E (APOE-ε4) has been associated with both sporadic and familial late-onset AD, and patients with mild cognitive impairment (MCI) due to AD are more likely to progressively deteriorate. Spatial navigation performance will be examined on a sample of 76 community-dwelling senior citizens (25 healthy controls; 25 individuals with subjective cognitive decline (SCD); and 26 patients with MCI due to AD) via a virtual computer-based task (i.e., the AppleGame) and a naturalistic task (i.e., the Detour Navigation Test—modified version) for which a wearable device with sensors will be used for recording gait data and revealing physiological parameters that may be associated with spatial disorientation. We expect that patients with MCI due to AD and APOE-ε4 carriers will show altered SN performances compared to individuals with SCD and healthy controls in the experimental tasks, and that VR testing may predict ecological performance. Impaired SN performances in people at increased risk of developing AD may inform future cognitive rehabilitation protocols for counteracting spatial disorientation that may occur during elders’ traveling to unfamiliar locations. The research protocol has been approved by the Ethics Committee of the Istituto Auxologico Italiano. Findings will be published in peer-reviewed medical journals and discussed in national and international congresses.

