### 1.7. Aim of the Study Protocol

The first endpoint of the research is to explore differences in SN performances among healthy older adults, individuals with SCD, and patients with MCI due to AD on a VR task (i.e., the “AppleGame”) and on a naturalistic task (i.e., the Detour Navigation Test-modified version, DNT-mv) using an innovative technological apparatus recording gait data and revealing physiological parameters that may be associated with SD.

The second endpoint of the research is to verify if examinees’ performances in such a well-characterized laboratory-based SN-testing task may predict impairment in a real-world context.

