### 2.4. Statistical Analysis

Data distribution will be first checked on collected variables by assessing skewness and kurtosis values, by performing normality and heteroscedasticity tests, and by visually inspecting histogram and Q–Q plots. Based on data meeting or non-linear model assumption, either parametrical or non-parametrical analyses will be performed. By means of the R marco *pwr* [86], the minimal sample size has been set as 76 participant, based on a power analysis for a multiple regression model that took into account the following parameters: α = 0.05; 1-β = 0.9; *f*^2^ = 0.15 (medium effect size, in order to be conservative) [87]; and numbers of predictors: 3 (age, APOE genotypes, and belonging to each group, with the last two predictors as dummy variables).

We will detect the route disorientation scores, i.e., WTs and MsH, as already described in Puthysserypaddy et al. [64]. Accordingly, all the violations in terms of deviations from the pre-established return path (i.e., movement at an intersection onto a different path as compared to the original one, or non-roadable walkways) will be written down by the experimenter as WTs in a pre-set paper grid for *Route A*. The overlaps with the *Route A* return path, and, likewise, non-roadable walkways will be written down by the experimenter as WTs in a pre-set paper grid for Route *B*. Further, we will detect the MsH as the participant either slows down/stops and looks around to aid orientation or verbally admits to the experimenter that he/she is unsure about his/her whereabouts, both for *Route A* and the *Route B* return path.

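### The second endpoint asks whether the VR task predicts real-world impairment, but the only analysis named is a one-predictor regression, which shows association and gives no measure of predictive accuracy

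*Protocol article*

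**What the plan says.** Section 1.7 (Aim of the Study Protocol) sets the second endpoint as verifying whether performance in the "laboratory-based SN-testing task may predict impairment in a real-world context".

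Section 2.4 (Statistical Analysis) gives one analysis that relates the two tasks with a direction: "a linear/generalized linear regression analysis will be run, taking into account the drop errors of the AppleGame subtasks". The subtasks are "considered one at a time", and the totals of wrong turns (WTs) and moments of hesitation (MsH) serve as outcomes. No covariate and no group term is named for this model, so as written it is fitted to all participants together. The section also states that "the minimal sample size has been set as 76 participant"; the Abstract splits them into "25 healthy controls; 25 individuals with subjective cognitive decline (SCD); and 26 patients with MCI due to AD".

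Section 3 (Discussion) repeats the expectation: "we assume that the drop errors obtained in the VR task may predict the route disorientation scores of the naturalistic task". It then goes further. It presents the AppleGame as a possible means of early diagnosis, says that it can predict real-life navigation impairment, and says that clinics should use it as a matter of routine.

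The article does not define impairment on the Detour Navigation Test (DNT-mv), name a measure of predictive accuracy, or state what result would count as meeting the endpoint.

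**The concern.** A regression slope that differs from zero shows that two scores are associated on average. It does not show how closely one person's real-world score can be told from that person's drop error, which is what a diagnostic or routine-use claim needs. Adding covariates, correcting for multiple tests or changing the sample size would still give a slope.

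Pooling makes the gap wider. The three groups are chosen to differ in navigation ability. If patients with MCI do worse on both tasks, a pooled slope can be significant although drop error says nothing beyond the diagnosis that the participant already carries.

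At stake is the conclusion: following the plan as written could lead to a statement that the VR task predicts impairment in individuals when only a weak or group-driven association has been shown.

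**Working it through.** **Inputs.** N = 76, α = 0.05 and f² = 0.15 from section 2.4; groups of 25, 25 and 26 from the Abstract. Assumed here: two-sided test, simple linear regression without covariates, bivariate normal scores.

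**The plan's own N.** Section 2.4 derives 76 from a three-predictor model (age, APOE, group) at power 0.90. Drop error is not in that model. Its inputs give N = 99 at power 0.90 and 77 at power 0.80; N = 76 has power 0.796. That is a separate matter. N = 76 is taken as given below.

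**Step 1: smallest significant correlation.** With t(0.975; 74) = 1.9925,

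r = t / √(t² + N − 2) = 1.9925 / √(3.970 + 74) = 0.226.

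The 95% CI by Fisher's z is about 0.00 to 0.43.

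**Step 2: predictive content at that value.**
- R² = 0.226² = 0.051.
- Fall in residual SD = 1 − √(1 − 0.051) = 0.026, or 2.6%.

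**Step 3: the same at the planning effect, read as one predictor.**
- R² = 0.15 / 1.15 = 0.130, so r = 0.36.
- Fall in residual SD = 1 − √(1 − 0.130) = 0.067, or 6.7%.

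**Step 4: discrimination.** The article defines no impairment, so a cut is assumed: the worst third on the DNT-mv. The AUC is the probability that a person in that third has a larger drop error than a person outside it. By simulation from a bivariate normal:

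| r | R² | Fall in residual SD | AUC, worst third |
|---|---|---|---|
| 0.226 | 0.051 | 2.6% | 0.60 |
| 0.36 | 0.130 | 6.7% | 0.67 |

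At r = 0.226 the AUC stays between 0.60 and 0.61 if the impaired share is set anywhere from 25% to 50%.

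**Step 5: what pooling alone can produce.** Suppose that the MCI group differs from the other two by d SD on both tasks, that healthy controls and SCD do not differ, and that the two scores are unrelated within groups. With p = 26/76 = 0.342, p(1 − p) = 0.225, and the pooled correlation is

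r = p(1 − p)d² / [1 + p(1 − p)d²].

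- d = 0.8: 0.144 / 1.144 = 0.13.
- d = 1.2: 0.324 / 1.324 = 0.24.

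In simulated samples of 76 the pooled slope was significant in 19% (d = 0.8) to 59% (d = 1.2). The values of d are assumptions; the article gives none.

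**The case against.** **No success criterion is written.** The article says only that a regression will be run. It names no p-value rule and does not exclude R² or prediction error. This stands: a reader might infer that a significant slope is the stated criterion, but the text does not say so. The threshold in Step 1 is therefore conditional.

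**An article leaves such detail to the full plan.** Validation methods and bootstrap intervals are often left there, and their absence alone would be no finding. But the article itself fixes the analysis and attaches an individual-level clinical claim to it. The mismatch between those two statements is in the text.

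***Predict* is ordinary regression language.** The Discussion frames the endpoint partly as a question about how virtual and real navigation relate, with hypotheses for particular subtasks and routes. Regression suits that question and remains valid for it. It does not carry the further step to diagnosis and routine use.

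**The slope may be as good as worthless out of sample.** This stronger reading is tempting, because at a true correlation of 0.226 the leave-one-out R² (against the full-sample mean) is zero or negative in about half of samples. It is not supported. About half of those samples have no significant slope. Among those that do, leave-one-out R² is zero or negative in only about 5%, and in almost none if the leave-one-out mean is the reference. With one predictor and 76 participants, overfitting is a small problem.

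**r = 0.23 is the minimum.** An observed association may be stronger, and readers would see its size. This stands too, which is why the planning effect is shown beside it. The threshold is exact only for simple linear regression; WTs are counts and may call for a generalized linear model.

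**The worst-third cut is not in the article.** Correct. It serves only to illustrate size.

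**Conclusion.** The point holds as a mismatch between question, analysis and claim. The named regression can show that AppleGame and DNT-mv scores are associated. It cannot by itself support the statement that the AppleGame predicts impairment in individuals or merits routine use.

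If a significant slope were taken as success, the bar would be low: 5% of variance explained and weak, though not absent, discrimination. An effect of the size used for planning would still discriminate only modestly. Because no group term is named, part or all of a significant slope could reflect differences between the diagnostic groups.

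The figures rest on a two-sided test, simple linear regression, bivariate normality and, for the AUC, an assumed cut. The regression is not wrong and the data need not change. The point concerns what is reported and what is concluded, and it should be addressed before the analysis.

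**What to change.** - Keep the regression in section 2.4.
- For the second endpoint, also report the explained variance or the prediction error of the DNT-mv score, with a bootstrap 95% CI.
- Report the cross-validated gain from adding drop error to a model with age and diagnostic group, with its CI.
- Use *predicts* only if the lower limit of that gain is above zero. Otherwise write *is associated with*.
- Soften the Discussion sentences on diagnosis and routine clinical use to match.
- An AUC is optional, and only with an impairment cut-off on the DNT-mv that the sponsor fixes before the data are analysed.

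The cost is a little more analysis on data that will be collected anyway. The gain over age and diagnosis is a stricter question than the endpoint now asks, so the claim may turn out less favourable.
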